## Abstract

**Introduction:**

Nicotine replacement therapy (NRT) helps pregnant women quit smoking. Usual National Health Service (NHS) cessation care in pregnancy starts only after women stop smoking and comprises behavioural support and NRT. NRT is stopped if women restart smoking. We hypothesised that NRT would have a bigger effect on cessation in pregnancy if used: (1) to reduce smoking before quitting (‘preloading’), (2) during brief smoking lapses after quitting and (3) to help those who cannot stop smoking, to reduce instead.

**Methods and analysis:**

A two-arm parallel group, open-label, multicentre, assessor-blind randomised controlled trial. Participants are recruited at hospital antenatal clinics and other NHS settings throughout England and Wales or via social media advertising. Those enrolled are in antenatal care, <25 weeks’ gestation, smoke ≥5 daily cigarettes; accept referral for NHS stop smoking support and agree to set quit dates, try NRT and vape less than daily. Participants are randomised to: (1) usual care (UC) or (2) UC plus an intervention combining (1) NRT for preloading, (2) counselling to continue NRT during brief smoking lapses, and for those who cannot stop, (3) NRT to reduce smoking. The primary outcome is biochemically validated, smoking abstinence from 6 weeks after randomisation to 36 weeks gestation. Secondary outcomes include birth outcomes and cost per quality-adjusted life year. Questionnaires collect follow-up data augmented by medical record information. We anticipate quit rates of 10% and 15.9% in the control and intervention groups (OR=1.7). By recruiting 1430 participants, smoking, nicotine and pregnancy 3 should have 90% power (alpha=5%) to detect this effect. We will use the Economics of Smoking in Pregnancy model to estimate cost-effectiveness.

**Ethics and dissemination:**

Ethics approval was granted by the West Midlands—Coventry & Warwickshire Research Ethics Committee (REC reference: 21/WM/0172; Protocol number 21001; IRAS Project ID: 291236). Written informed consent will be obtained from all participants. Findings will be disseminated to the public, funders, relevant practice and policy representatives and other researchers.

**Trial registration number:**

ISRCTN84798566.

STRENGTHS AND LIMITATIONS OF THIS STUDYThis randomised controlled trial is testing an intervention to enhance smoking cessation care for pregnant women, where pregnant women will be offered nicotine replacement therapy: (1) to reduce smoking before quitting (‘preloading’), (2) during brief smoking lapses after quitting and (3) to help those who cannot stop smoking, to reduce instead.The trial design is explanatory and pragmatic and thereby will show whether changes in smoking are due to the intervention.Trial design is reported according to the Standard Protocol Items: Recommendations for Interventional Trial guidelines.Participants are not blind to the treatments; we will aim to limit this bias by using biochemical validation of abstinence as the primary outcome.Obtaining data on smoking status in pregnancy is difficult; using routine data may help improve this.

## Introduction

 Smoking in pregnancy (SIP) is the biggest reversible cause of miscarriage, stillbirth, prematurity, low birth weight (LBW), perinatal, neo-natal, sudden infant death and poorer infant cognition and behavioural outcomes.^1^,^3^ Stopping SIP reduces LBW and neonatal intensive care admissions, resulting in healthier babies.^4^ SIP is a major international public health problem; in high-income countries, prevalences are between 13% and 25%,^5^,^8^ and a similar epidemic is developing in low- and middle-income countries.^9^ In England in 2017/2018, when this study was planned, 11% of women were smoking at childbirth with rates highest in economically deprived areas (Blackpool 26%).^10^ This translated to around 94 600 SIP-exposed fetuses annually in England and Wales.

Nicotine replacement therapy (NRT) is effective for smoking cessation in pregnancy (risk ratio (RR; 95% CI) for stopping with NRT compared with control 1.41 (1.03 to 1.93))^11^ and is very probably safer than smoking.^11 12^ However, NRT appears to have more impact on quitting by non-pregnant smokers (RR (95% CI) 1.55 (1.49 to 1.61)). This disparity is likely explained by pregnancy-related acceleration in nicotine metabolism, which means higher nicotine doses are needed to prevent cravings, and so help pregnant users to abstain.^13 14^ As NRT is one of the few treatments that can be used in pregnancy and is offered to pregnant women by all UK Stop Smoking Services (SSS),^15^ seeking ways to maximise NRT effectiveness is imperative.

Outside of pregnancy, NRT helps more people to stop smoking when, used as ‘preloading’, ‘smoking reduction’ or ‘lapse recovery’. ‘Preloading’ involves using NRT, such as a nicotine patch, while still smoking and preparing for a quit date (QD) in 2–4 weeks; this improves smoking abstinence at 6 months compared with usual care (UC) (RR (95% CI) 1.25 (1.08 to 1.44))^16^ and effects may persist for longer.^17 18^ ‘NRT smoking reduction’ comprises using NRT to smoke fewer cigarettes; without necessarily intending to quit, those who try this are more likely to subsequently stop smoking completely compared with those who try to reduce without NRT (RR (95% CI) for cessation 1.87 (1.43 to 2.44)).^19^ NRT is used as ‘lapse recovery’ during brief lapses to smoking or ‘slip ups’ that occur after the QD. NRT lapse recovery consists of continuing rather than stopping NRT during these slip ups. With NRT lapse recovery, quitters who lapse are more likely to return to complete abstinence. A secondary analysis from a placebo-controlled randomised controlled trial (RCT) found that quitters who used NRT rather than placebo during lapses were more likely to be abstinent 6 or 10 weeks later ((8.3% vs 0.8%; RR, 11.0, 95% CI (2.59 to 48.72) and (9.6% vs 2.6%; RR, 3.7, 95% CI (1.61 to 8.43)), respectively.^20^ Additionally, a trial testing NRT for lapse recovery found a non-significant 5% higher 4-month quit rate (51% vs 46%) in those who used NRT in brief smoking lapses.^21^

NRT used as ‘preloading’ or ‘smoking reduction’ outside of pregnancy results in lighter smoking and less exposure to tobacco smoke toxins.^22^ Studies investigating concurrent NRT use and smoking by pregnant women suggest that both uses of NRT would reduce smoking and tobacco smoke toxin exposures in pregnancy too. During the ‘titration’ phase of an RCT testing nicotine patches for quitting in pregnancy,^23^ participants used NRT patches to cut down smoking. Compared with when smoking, women who used NRT patches but still smoked, used fewer weekly cigarettes (mean difference (MD) −48, 95% CIs −52 to −38) and exhaled less carbon monoxide, CO (MD −3 ppm, 95% CI −4 to − 2ppm) but had similar cotinine concentrations (118 ng/mL vs 111 ng/mL, MD (ratio of) geometric means, 0.94, 95% CIs 0.83 to 1.07).^24^ Similarly, from a cohort of 32 women who were in the first month after quitting, 24 submitted daily reports of NRT use and smoking heaviness to a self-monitoring app. In the 17 who admitted both using NRT and smoking on at least 1 day, we found a strong, inverse relationship between smoking heaviness and NRT dose on those days^25^; for each 10 mg increase in nicotine from NRT, the daily number of cigarettes smoked fell by 0.6 (24% reduction).

### Rationale

Despite the promising findings in non-pregnant populations, we could find no trials conducted in pregnant people, which investigated the effectiveness of NRT used for preloading, lapse recovery or for smoking reduction. Hence, in smoking, nicotine and pregnancy 3 (SNAP3), we combined all three NRT uses into a single intervention and tested the effectiveness and cost-effectiveness of adding this to UC, as compared with UC alone. In this paper, we report the protocol for the SNAP3 Trial, according to the Standard Protocol Items: Recommendations for Interventional Trial guidelines.^26^

## Methods and analysis

SNAP3 is a two-arm, parallel, open-label, individually RCT recruiting from antenatal settings and via online advertising.

### Objectives

#### Primary objective

To compare the effectiveness of UC plus enhanced support for preloading and lapse recovery and NRT offered for preloading, with UC alone for promoting prolonged smoking cessation in pregnancy.

#### Secondary objectives

To investigate the incremental cost-effectiveness of UC plus enhanced support for preloading and lapse recovery and NRT offered for preloading, with UC alone for prolonged smoking cessation in pregnancy.To compare the effects of UC plus enhanced support for preloading, lapse recovery and smoking reduction and NRT offered for preloading and smoking reduction with UC alone on:Validated 7-day abstinence from smoking in late pregnancy.Reported 50% reduction in smoking.Exhaled CO at delivery.Maternal, fetal and neonatal birth outcomes.

### Eligibility criteria

#### Inclusion criteria

Pregnant people of any age are eligible if they are <25 weeks’ gestation; have been referred for or have been receiving antenatal care; smoke ≥5 daily cigarettes; are willing to set a QD and accept referral to SSS; are willing to use NRT patch to try to stop smoking; are able to understand written and spoken English and have the capacity to give informed consent.

#### Exclusion criteria

People are not eligible if they are already in a cessation study; have absolute contraindications to NRT use such as known severe reaction/hypersensitivity to NRT, recent cardiovascular/cerebrovascular event or changes and taking theophylline/clozapine; or currently use and intend to continue to use e-cigarettes every day.

### Recruitment

Participants will be identified from National Health Service (NHS) clinical settings in England and Wales, or via online advertisement outside of the NHS settings. A list of all trial sites can be found here: https://www.isrctn.com/ISRCTNISRCTN84798566.

#### Participant identification

##### NHS settings

NHS settings can include hospital antenatal care, community midwifery care, general practice (GP) or SSS settings. NHS settings can be sites where staff identify and recruit participants or ‘patient identification centres’ where site staff identify potential participants who are then offered enrolment by the central trial team. The site principal investigator (PI) can be a clinician or a research midwife/nurse.

Potential participants can be identified from patient records and lists of women booked for antenatal care/clinics or referred for smoking cessation; staff can approach patients as they attend appointments or by telephone, letter, email or text. Posters advertising the study, with a link to the patient information sheet (PIS) and research team’s contact details, can be displayed in surgeries and clinics.

Screening questionnaires and summary leaflets can be distributed to potential participants by post or electronically to facilitate approaches described above. These can help identify pregnant people eligible for study entry. Potential participants interested in joining the study may provide their contact details either using wet-ink screening questionnaires or electronically, via a link to a secure REDCap database, hosted by the University of Nottingham.

GPs can send text messages containing similar links to potential participants identified via periodic medical record searches.

NHS settings may also use digital advertisements on their social media, electronic patient notes and websites; these include links to the study PIS and screening questionnaires.

##### Online advertisement outside of the NHS settings

Digital advertisements with an embedded link to the electronic screening questionnaire, targeted at people who are pregnant and smoke, will be published periodically on Google and social media, such as Facebook. Potential participants who complete the screening questionnaire will receive a text and/or an email with the link to the PIS and consent form. The research team will contact them over the telephone to answer any questions, discuss eligibility and to consent them to the study.

### Consent

Consent can be obtained by the PI or delegate, either face to face or over the telephone, using wet-ink or electronic consent form, as appropriate. An electronic consent form is generated by the researcher via a secure REDCap database; participants will be able to sign electronically on a device, such as a mobile phone or a computer. Verbal telephone consent via REDCap generated form can be obtained if the participant is unable to access the electronic consent form. A strict protocol will be followed for all consent procedures, and copies of consent will be shared with the participant. Subsequently, letters will be sent to all participants’ GPs to inform them of the study enrolment.

### Randomisation and blinding

Once informed consent is documented, the researcher will collect baseline data, before randomising the participant to either the intervention or control group in a 1:1 ratio, using the Nottingham Clinical Trials Unit’s web-based randomisation system. The randomisation schedule is stratified by site and level of nicotine addiction and is based on a computer-generated pseudo-random code using random permuted blocks of varying size.

Participants will be aware of their treatment allocation, but researchers who collect primary outcome data will be blinded. Staff randomising participants will not be blinded to treatment allocation, as they will need to ensure participants in each group receive relevant treatment information and referral, if required.

The trial statistician will remain blinded prior to database lock and will be unblinded prior to conducting the final analysis.

### Intervention

With no restriction on treatments used, we will offer participants in both groups the usual NHS stop smoking support available to them. The components and intensity of cessation support available vary across localities.

#### Usual care

##### Postenrolment

After randomisation, as per standard NHS practice, recruiting staff will provide ‘Very Brief Smoking Advice on Smoking for Pregnant Women**’** (VBA), as defined by the National Centre for Smoking Cessation Training (NCSCT).^27^ Staff are trained to NCSCT standards and VBA comprises:

Exhaled air CO monitoring,Advice that intensive behavioural support increases chances of quitting, andReferral for this*,* or other available NHS support.

Participants will also be provided with a standard smoking cessation leaflet, “Smoking and your baby: advice for parents”, which comprises advice on stopping smoking and creating smoke-free environments as well as help in finding local NHS support to stop smoking.

##### Referral for NHS stop smoking support

After being enrolled and receiving VBA, participants will be referred for locally available NHS stop smoking support, which can be offered at hospitals, GP surgeries, pharmacies or from helplines, and we note the characteristics of support offered in different areas. Details for the NHS Smokefree Website, which is a further source of support and advice, will also be provided.

In most study areas, participants can access intensive behavioural support delivered by NHS stop smoking practitioners (SSPs), which follows NCSCT guidance and contains these common components^3 28^:

Help setting a QD,Face-to-face or telephone/video counselling, andNRT starting on a QD when smoking abstinence begins.^15 29^

Letters will be sent to GPs, informing them of participants’ enrolment in the study and asking them to consider prescribing cessation-orientated NRT as per current NICE guidance if participants request this.

In usual NHS support, NRT is used for cessation only, and not for smoking reduction or preloading; quitters are advised to stop NRT if they re-start smoking.

### Intervention

The study intervention comprises three components delivered by dedicated SNAP3 SSPs, trained to the required NCSCT standard for delivering stop smoking support in the UK NHS.^30^ For NRT, Nicorette Invisipatch 15 mg/16 hours patch and Nicorette 15 mg inhalator will be used.

#### Component 1: preloading

Preloading advice will be delivered before participants try stopping smoking (before QD), and comprise:

Up to 4 sessions of preloading counselling,^17^ tailored for pregnancy.For 1–4 weeks before a QD, a daily 15 mg/16 hours nicotine patch.A hard copy preloading leaflet with links/QR code to an identical online version; this comprises information on benefits of using NRT patches for preloading, safety of NRT, advice on how to use NRT patches for preloading and after QD, managing cravings, lapse recovery and study team contact details.Personalised text messages reinforcing preloading principles.

In the first counselling session, SSPs will discuss concerns about nicotine and NRT side effects and help participants set a QD for between 1 and 4 weeks’ time. While in previous studies, preloading participants were advised to wear the NRT patch while smoking as usual,^17^ in SNAP3 participants will be counselled to preload by wearing NRT patches and reducing daily smoking in the run up to their QD. Up to three more weekly counselling sessions will be offered, with the total number corresponding to time spent preloading. Each week, SSPs will send participants an average of two personalised motivational/adherence enhancing texts and one consultation reminder. In localities where further NHS stop smoking support is available, after the first preloading session, SSPs will refer participants for follow-on cessation support, aiming for continuity of treatment. Where there is no local NHS cessation-orientated support, SSPs will advise participants to contact their midwife, pharmacy or GP and inform participants about the NHS Smokefree Website.

#### Component 2: lapse recovery counselling

During the preloading period, SSPs will also advise participants to continue NRT during any brief lapses to smoking that may occur after their QDs. If lapses persist for 14 or more days or participants smoke more than 5 cigarettes for 3 or more days, participants will be advised to stop using NRT, end the quit attempt and contact their local NHS stop smoking support for help making a new quit attempt.

The leaflet, website and personalised texts described above will be used to reinforce lapse recovery counselling messages.

#### Component 3: NRT for smoking reduction

At 6 weeks postrandomisation, participants who still smoke despite being offered the first two intervention components and/or NHS support to stop smoking will be offered referral for NHS stop smoking support. Those who decline will be offered the third intervention component, NRT for smoking reduction.

The aim of this component is for participants to reduce their smoking such that they smoke fewer cigarettes than at enrolment and fewer than 10 daily cigarettes (whichever is the lowest); infants’ birth weight reductions are greatest below this smoking intensity.^31^

This intervention component comprises:

Biweekly telephone or video counselling to use NRT for smoking reduction.2 week supplies of Nicorette Invisipatch 15 mg/16 hours nicotine patches or Nicorette 15 mg NRT inhalator cartridges (up to 6 daily) until childbirth, contingent on sufficient smoking reduction.A hard copy reduction leaflet with links/QR code to an identical online version.Text messages reinforcing reduction principles.Use of a bespoke smartphone app, called ‘MyNRT’, for self-monitoring smoking and NRT use.

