**Figure 1 F1:**
[figure not shown]
Schedule of data collection and intervention delivery time points. ^a^Participants who accepted component 3 of the intervention—Reduction. ^b^CO reading collected directly during face-to-face appointment or from a recent antenatal appointment record. ^c^Intervention group only, until approximately 30 paired samples obtained. ^d^Validation sample, only collected from participants who reported not smoking in the last 7 days. ^e^Intervention group only. CO, carbon monoxide; NRT, nicotine replacement therapy; SSS, Stop Smoking Services.

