#### Offering NRT for smoking reduction

We will aim to offer the third intervention component to all intervention group participants who are smoking and not interested in trying to quit. Hence, if follow-up is by telephone, we will offer this during the call; alternatively, we will contact those participants who report smoking in their responses to online questionnaires. Those who accept NRT for help with smoking reduction, and for whom there is no baseline saliva sample, will be asked to provide one before they start using NRT for reduction.

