#### 36 weeks gestation (or childbirth, if earlier)

We will ask about smoking behaviours and quit attempts, NRT and e-cigarette use, use of stop smoking support and about relevant cost data. We will attempt to collect saliva samples from all who report abstinence from smoking for at least 7 days. Samples will be requested postally (see above) or at hospital attendance and before collection we will ask, by questionnaire or verbally, about smoking and recent use of NRT or e-cigarettes.

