### Patient and public involvement

A patient and public involvement (PPI) group has been involved in the trial design and throughout the study duration. The group consists of women who had experience of smoking during pregnancy. In the early stages of the intervention design, we interviewed five PPI group women who had experience of pregnancy and smoking. We discussed the proposed components and made changes to the intervention based on the comments and ideas brought by the PPI group. All interviewed thought NRT use for preloading and lapse recovery can be beneficial for pregnant people who wish to try and stop smoking. However, there was some concern about allowing women to use NRT throughout pregnancy without any focus on abstinence. In response to this point, the third intervention component was amended such that researchers will monitor participants’ heaviness of smoking and will stop NRT provisions if women admit smoking more heavily than at baseline or >10 daily cigarettes. This change was made to ensure a focus on reducing smoking when using NRT, rather than on ‘smoking as normal’.

During study set-up, representatives of the PPI group are being consulted on all aspects of the study, such as acceptability and accessibility of participant-facing documents, recruitment and retention methods, methods of data collection and the dissemination of findings. To ensure PPI involvement in the project’s strategic direction, two PPI representatives independent from the study team are invited to attend each TSC meeting.

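### The self-reported ≥50% smoking reduction outcome at 36 weeks is at risk of bias towards the intervention, because only intervention women can have an NRT supply that depends on what they admit smoking

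*Protocol article*

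**What the plan says.** All references are to the protocol article.

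- **Who gets component 3.** The aim is to "offer the third intervention component to all intervention group participants who are smoking and not interested in trying to quit" (Offering NRT for smoking reduction). The offer follows the 6-week follow-up: it is made in the telephone call, or by contacting women whose online answers show that they smoke.
- **What supply depends on.** Two-week supplies run "until childbirth, contingent on sufficient smoking reduction". The stated aim is that "they smoke fewer cigarettes than at enrolment and fewer than 10 daily cigarettes (whichever is the lowest" (Component 3). The patient and public involvement section says that researchers monitor heaviness of smoking and "will stop NRT provisions if women admit smoking more heavily than at baseline or >10 daily cigarettes".
- **Control arm.** In usual NHS support, "NRT is used for cessation only, and not for smoking reduction or preloading" (Referral for NHS stop smoking support).
- **Outcome.** "Reported 50% reduction in smoking" is a secondary objective comparing the whole package, component 3 included, with usual care. The smoking-related secondary outcomes define it as a reported cut of at least 50% in daily cigarettes at 36 weeks.
- **Validation at 36 weeks.** "We will attempt to collect saliva samples from all who report abstinence from smoking for at least 7 days". The Figure 1 legend agrees: "Validation sample, only collected from participants who reported not smoking in the last 7 days".
- **Blinding.** Participants know their allocation. Assessor blinding is stated for those who collect primary outcome data (Randomisation and blinding).

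**The concern.** The outcome that component 3 targets most directly is a count given by the participant. A woman on component 3 may still be receiving NRT at 36 weeks, on a condition judged by what she admits smoking. A control woman has no reduction supply to protect. If some women shade their count downwards for this reason, the error falls in one arm and in one direction.

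The plan's stated protection against open-label bias is biochemical validation of abstinence as the primary outcome. That does not reach a woman who reports cutting down but still smokes, because no study saliva is sought from her at 36 weeks. Blinding the assessor does not help either, since the error arises with the participant. A reported reduction could then be read as reduced smoking when part of it is changed reporting.

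**Working it through.** **Plan's own figure.** An odds ratio of 1.70 on a 10% control rate gives 0.15888. The two-proportion formula at 90% power and 5% two-sided alpha gives 682 per arm, and 715 with a continuity correction, which is the stated number. The concern does not touch it; 715 per arm is used below only as the size of each arm.

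**Step 1: is the supply condition the same as the outcome?** For each baseline count, the table gives the highest whole daily count that meets the component 3 aim (below enrolment and below 10), the highest that avoids the stop in the patient involvement section (not above baseline and not above 10), and the count needed for a 50% cut.

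| Baseline/day | Component 3 aim | Patient involvement section | 50% cut |
|---|---|---|---|
| 5 | 4 | 5 | 2.5 |
| 10 | 9 | 10 | 5 |
| 15 | 9 | 10 | 7.5 |
| 18 | 9 | 10 | 9 |
| 20 | 9 | 10 | 10 |
| 25 | 9 | 10 | 12.5 |

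Any count that keeps supply also scores as a 50% cut from a baseline of 18 (9 = 18/2) under the first text and 20 (10 = 20/2) under the second. Below that, a woman can keep her supply without reporting a 50% cut, so the incentive to report less acts on the outcome only indirectly. Entry is at 5 or more a day, and the article gives no baseline distribution.

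The two middle columns also differ. A woman smoking exactly her baseline number, or exactly 10 a day from a baseline of 10 or more, misses the component 3 aim but is not stopped under the other text.

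**Step 2: how large could the bias be?** The article gives none of these inputs; all are assumptions:
- r, the true proportion with a ≥50% reduction, equal in both arms: 30–50%
- c, the share of the intervention arm on component 3 at 36 weeks: 10–40%
- m, the share of true non-reducers on component 3 who falsely report a ≥50% cut: 5–30%

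With honest controls and no true effect, false difference = c × m × (1 − r). The chance of a significant result is for an unadjusted two-sided 5% test with 715 per arm.

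| r | c | m | False difference (points) | Odds ratio | Chance of p<0.05 |
|---|---|---|---|---|---|
| 50% | 10% | 5% | 0.25 | 1.01 | 5.1% |
| 40% | 20% | 10% | 1.2 | 1.05 | 7.5% |
| 40% | 20% | 20% | 2.4 | 1.10 | 15.2% |
| 40% | 40% | 20% | 4.8 | 1.22 | 45.1% |
| 30% | 40% | 30% | 8.4 | 1.45 | 91.8% |

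Middle case: 0.20 × 0.10 × 0.60 = 0.012, or 1.2 points. The standard error at 40% is √(2 × 0.4 × 0.6/715) = 2.6 points, so that bias is about half a standard error.

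**The case against.** The strongest reply is that nothing says the 36-week answer decides supply. Component 3 is delivered by dedicated practitioners through biweekly counselling, while follow-up is sought first by online questionnaire. A reader might infer that the 36-week questionnaire is itself the supply check; the article does not say so. What remains is that the same article has follow-up answers trigger the NRT offer at 6 weeks and names researchers as those who monitor smoking. A woman could reasonably think that her answers count.

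A reader might also infer that the comparison is biased as a matter of fact. Step 1 does not support that: the supply condition is not a 50% cut, and only women who accept component 3 are exposed.

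Controls are not wholly free of incentive, since usual care advises stopping NRT on a return to smoking. But usual care is offered in both arms, so this does not clearly offset an added condition in one.

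An objective comparison already exists: exhaled CO at delivery is a between-arm secondary outcome, and women on component 3 give CO and saliva at 8–12 weeks. This stands and reduces the seriousness. However, the 8–12 week samples come from one arm, and the article does not tie the reported reduction to CO.

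The remark in Analyses that this is the first such study in pregnancy concerns the offering of NRT for reduction within a trial. It should not be read as a claim about this outcome, which compares the full package with usual care and cannot isolate component 3.

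Finally, supportive analyses and questionnaire wording often sit in the SAP or full protocol, which are not shown. Their absence here is not the point. The point is the combination that the article does fix: a one-arm supply condition based on report, a report-only outcome, and validation limited to women claiming abstinence.

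**Conclusion.** The point holds as a risk of differential misreporting in one secondary outcome. If the incentive acts, it favours the intervention. It bears directly on the outcome from about 18–20 cigarettes a day at baseline and indirectly below that. Its size cannot be determined from the article: the range of 0.25 to 8.4 points, from negligible to large, rests wholly on assumed uptake, misreporting and true reduction rates.

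The primary outcome is not affected by this route. It is biochemically validated, and the sample size section states that component 3 does not contribute to it. The matter is worth correcting because the remedy is cheap and relies on data already sought.

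The boundary difference between the two supply descriptions is a separate, minor inconsistency.

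**What to change.** 1. Open the 36-week questionnaire or call, identically in both arms, with a statement that the answers are for research only and do not affect NRT supply, and make sure that this is true in practice. By 30 September 2025, 930 of 1430 women had been enrolled, so at least 500 (1430 − 930) 36-week contacts were still to come.
2. Pre-specify, before unblinding, a supportive analysis in both arms: reported reduction of at least 50% together with an exhaled CO at 36 weeks or delivery below the enrolment CO. The Baseline and After childbirth sections already seek these readings. Report it beside the self-reported result and the planned CO-at-delivery comparison, with the number of women lacking CO in each arm. Saliva cotinine is a poor substitute: the Introduction reports similar concentrations with patches plus smoking and with smoking alone (118 and 111 ng/mL), while cigarettes and CO fell.
3. State in advance that a self-reported effect not mirrored in CO will be described as reported reduction only.
4. Reconcile the supply condition in the component 3 section with that in the patient and public involvement section.

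The cost is one statement at a contact that already takes place, one extra analysis and an interpretation rule. The drawback is that CO from records will be incomplete and reflects only recent smoking, so the supportive analysis will include fewer women and be imprecise.
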